## Abstract

**Introduction:**

Shoulder pain due to irreparable rotator cuff tears can cause substantial disability, but treatment options are limited. A balloon spacer is a relatively simple addition to a standard arthroscopic debridement procedure, but it is costly and there is no current randomised trial evidence to support its use. This trial will evaluate the clinical and cost-effectiveness of a subacromial balloon spacer for individuals undergoing arthroscopic debridement for irreparable rotator cuff tears.

New surgical procedures can provide substantial benefit to patients. Good quality randomised controlled trials (RCTs) are needed, but trials in surgery are typically long and expensive, exposing patients to risk and the healthcare system to substantial costs. One way to improve the efficiency of trials is with an adaptive sample size. Such methods are well established in drug trials but have rarely, if ever, been used in surgical trials.

**Methods and analysis:**

Subacromial spacer for Tears Affecting Rotator cuff Tendons: a Randomised, Efficient, Adaptive Clinical Trial in Surgery (START:REACTS) is a participant and assessor blinded, adaptive, multicentre RCT comparing arthroscopic debridement with the InSpace balloon (Stryker, USA) to arthroscopic debridement alone for people with a symptomatic irreparable rotator cuff tear. It uses a group sequential adaptive design where interim analyses are performed using all of the 3, 6 and 12-month data that are available at each time point. A maximum of 221 participants will be randomised (1:1 ratio), this will provide 90% power (at the 5% level) for a 6 point difference in the primary outcome; the Oxford Shoulder Score at 12 months. A substudy will use deltoid-active MRI scans in 56 participants to assess the function of the balloon. Analysis will be on an intention-to-treat basis and reported according to principles established in the Consolidated Standards of Reporting Trials statement.

**Ethics and dissemination:**

NRES number 18/WM/0025. The results will be disseminated via peer-reviewed publications, presentations at conferences, lay summaries and social media.

**Trial registration number:**

ISRCTN17825590

Strengths and limitations of this studyMulticentre randomised trial of a subacromial spacer balloon following debridement, compared with debridement alone, for irreparable rotator cuff tears of the shoulder.Participant-assessor blinding, including blinded operation notes with novel unblinding mechanism.Mechanistic MRI substudy of 56 participants with images at 8 weeks and 6 months after surgery.Statistical adaptive design, with hard stopping rules for futility or efficacy based on emerging outcomes.

## Introduction

### Subacromial spacer balloons

Shoulder pain is a common and disabling problem. The UK population prevalence of shoulder pain is approximately 16%.^1^ Rotator cuff disease accounts for 70%–85% of this.^2–4^ People with a symptomatic rotator cuff tear typically have pain, restricted movement, loss of strength and disability. The condition is associated with substantial expense to society through both costs of treatment and loss of work (both paid and unpaid).^5–8^ Rotator cuff repair is a widely accepted treatment for symptomatic rotator cuff tears.^9 10^ Some tears cannot be surgically repaired, these are called irreparable tears.

Symptomatic irreparable rotator cuff tears are a challenging condition to treat. Treatment options including physiotherapy, injections, arthroscopic debridement, partial repair, muscle transfers, interposition grafts and even shoulder replacements.^11–14^ Arthroscopic debridement is commonly used and case series suggest it may be beneficial, but it remains a controversial option, with little randomised controlled trial (RCT) data on its use in the irreparable tear population.^15–17^

In 2013, the InSpace subacromial balloon spacer (Stryker, Michigan, USA) was introduced into UK orthopaedic practice as a potential treatment option for people with irreparable tears of the rotator cuff. In May 2016, an interventional procedure guidance document was published by the UK National Institute for Health and Care Excellence (NICE), which found that there was very limited evidence for its use. Therefore, the device was limited to research use only and a recommendation was made to assess its effectiveness.^18^ It has not yet received US Food and Drug Administration clearance in the USA, but it is a widely used treatment elsewhere in the world.

The InSpace device is a saline-filled balloon made of biodegradable (dissolvable) synthetic material. It is inserted above the main joint of the shoulder at the end of an arthroscopic debridement after an irreparable tear has been identified. It is simple to deploy and adds relatively little time to the operation.^19 20^ It cushions the humerus from pressing on the bone above it (the acromion) when the deltoid is active and during abduction of the arm, potentially reducing pain. It may also assist in the biomechanics of the shoulder, resisting proximal migration of the humerus under deltoid activity. The device begins to degrade and deflate from 3 months after surgery. During this time, it is thought to improve rehabilitation of the remaining rotator cuff and deltoid, so that when the device deflates, the biomechanics of the shoulder are better preserved.

The safety of the device in rodents has been established, with only one adverse event (AE): a fibrosarcoma that was thought to be unique to rodents.^21^ Proof of concept has been established in a series of 24 irreparable cuff tear cases in Slovakia in 2012, with 5-year follow-up results published in 2016.^22 23^ The device has been used in a number of centres across the UK, with multiple conference abstracts from the UK.^24–26^ These have demonstrated improvements in outcomes from baseline. Complications such as balloon displacement and non-cyst forming synovitis have been reported in a small number of cases (3 out of 61). One retrospective non-randomised study of 23 patients (12 with the balloon) showed an improvement in outcomes compared with debridement alone.^27^ There are no completed RCTs.

The benefits found in case series may not be unique to the InSpace balloon, although the relative effectiveness of the balloon in comparison to non-operative care or acromioplasty is not known and it could give substantial improvements.^17^

There is one other RCT in progress for this device—a company funded study in the USA which will recruit 184 participants, comparing partial cuff repair with balloon as a stand-alone intervention. Results are expected in mid-2020. Partial cuff repair is not a technique that is widely used in the UK and is not an appropriate comparator in a UK context.

### Trial designs in new surgical procedures

The safe introduction of new surgical procedures are essential to the delivery of high quality surgical care for patients. New procedures can result in a step-change improvement in treatment, but also introduce new risks and substantial costs. Major harm can be done when a misunderstood or well-intentioned intervention is used widely across the health service before it is formally evaluated.^28 29^

While pharmaceuticals must undergo rigorous clinical trials before introduction, this is not the case for surgical procedures.^30^ When surgical procedures are assessed rigorously, studies tend to be large multicentre, randomised trials which typically need to recruit over extended time periods.^29 31^ Improvements in the efficiency of delivering trials of surgical interventions would provide earlier answers to these important clinical questions, providing benefits to patients and making better use of healthcare resources.

The use of adaptive trial designs has been encouraged by major journals, the US Food and Drug Administration, and National Institute of Health Research panels.^32–34^ Adaptive trial designs allow prospectively planned modifications, such as stopping the study early or dropping an intervention, based on emerging findings as the trial proceeds, while preserving the scientific validity and integrity of the trial. This flexible strategy typically reduces costs and shortens time scales, without compromising the integrity, statistical power or rigour of the study.^32 35–37^

In this trial, we are using a novel statistical adaptive design approach for the assessment of a new surgical procedure. The statistical principles are laid out in a 2019 methodology paper.^38^ Briefly, the design uses early (3 and 6-month Oxford Shoulder Score, OSS) endpoint data to support emerging outcome data for the primary endpoint (12-month OSS) to make decisions about stopping for either futility or efficacy at preplanned interim analyses that occur before the end of recruitment. In the current study, we will apply these design principles to a multi-centre clinical trial of a new surgical procedure.

### Aim

To assess the clinical effectiveness, cost-effectiveness and safety of a subacromial spacer balloon for patients with symptomatic irreparable tears of the rotator cuff.^18^

## Methods

### Trial design

The Subacromial spacer for Tears Affecting Rotator cuff Tendons (START) study is a participant and assessor blinded, adaptive, multicentre RCT based in the UK comparing arthroscopic debridement using the InSpace balloon to arthroscopic debridement alone, performed using the Randomised, Efficient, Adaptive Clinical Trial in Surgery (REACTS) framework.

### Patient and public involvement

Patient involvement has been a core part of the design and delivery of the study, and will remain so, including in the interpretation and dissemination of results. In the planning stages, we engaged with multiple patients who had previously undergone rotator cuff surgery and their insights helped establish the design of the study, especially the outcomes. We reviewed patient facing materials with many shoulder patients before they were finalised. One of the coauthors is a patient and represents the patient view in trial management meetings, two patients sit on our steering committee. We will produce patient and public-focused summaries of the research and disseminate this widely.

### Objectives

#### Clinical objectives

Our primary clinical objective is to quantify and draw inferences on observed differences between arthroscopic debridement of the subacromial space and arthroscopic debridement with insertion of the InSpace balloon (Stryker, Michigan, USA) 12 months after surgery, using the OSS as the primary outcome measure.^39 40^

Secondary clinical objectives

To quantify and draw inferences on observed differences between arthroscopic debridement and arthroscopic debridement with insertion of the InSpace balloon (Stryker, Michigan, USA) on: shoulder function; patient-reported outcome measures; AEs and resource use at 3, 6 and 12 months.To perform an economic analysis, assessing the comparative cost-effectiveness of the two treatments.To compare the acromio-humeral distance on MRI scans in a sample of participants with and without the balloon at 8 weeks and 6 months after treatment, to assess the proposed mechanism of action of the balloon when it is still inflated (at 8 weeks) and to determine if the effect persists when it has deflated (at 6 months).

#### Methodological objectives

The primary methodological objective is to develop and implement appropriate statistical tools to allow an efficient adaptive clinical trial design, with the potential for early stopping for either futility or efficacy, using OSS data available at 3, 6 and 12 months.^38^

### Ethics, registration and oversight

The trial will conform to the principles of the Declaration of Helsinki and to MRC Good Clinical Practice guidelines. It will also comply with all applicable UK legislation and University of Warwick Standard Operating Procedures (SOPs). Trial oversight is provided by a data monitoring committee (DMC) and trial steering committee (TSC), both are made up of a majority of independent members and are conducted according to Warwick SOPs. Monitoring and audit will be undertaken by the sponsors according to a monitoring plan. The trial received full research ethical approval (RES number 18/WM/0025) on 13 February 2018, prior to commencing recruitment which is ongoing. Amendments will be communicated to sites by the coordinating team.

### Outcome measures

#### Primary outcome

The OSS at 12 months. The original study design was based around the Constant score, however the trial management group decided in March 2020, in light of the coronavirus outbreak, to revise this to the OSS. As the Constant score is a face-to-face measure usually taken in hospital clinics, it would have exposed participants to unnecessary risk during the height of the pandemic. The decision was agreed by both the TSCs and DMCs prior to the change.

The OSS has been well validated and used in high-impact randomised trials previously, it correlates well with the Constant score, both are similarly responsive and have comparable effect sizes in rotator cuff pathology.^39–43^ Based on our meta-analysis of outcomes for randomised trials, shoulder scores typically reach a plateau at 12 months after any intervention for a rotator cuff tear.^44^ The 24-month scores do not give sufficient additional value to justify the increase in costs and delay in the trial result that would be required had 24 months been used as the primary outcome.

#### Secondary outcomes

The OSS at baseline, 3, 6 and 24 months.The Constant Score at baseline, 3, 6 and 12 months. A standardised protocol for the objective component of the score has been developed based on the work of Moeller *et al* with training provided for all sites.^45–47^
Range of pain-free movement of the shoulder at baseline, 3, 6 and 12 months measured using a long-arm goniometer (12 ½”).Strength of shoulder abduction and flexion at baseline, 3, 6 and 12 months measured using a supplied IsoForceControl EVO_2_ dynamometer (Herkules Kunstoff, Switzerland).Western Ontario Rotator Cuff (WORC) index at baseline, 3, 6, 12 and 24 months.^48^
Health utility assessed using 5-level EuroQol 5 dimension score (EQ-5D-5L) at baseline, 3, 6, 12 and 24 months.^49 50^
Healthcare resource collected at 3, 6 and 12 months.Patient Global Impression of Change (PGIC) score, collected at 3, 6, 12 and 24 months. A simple 7-point scale assessing perception of improvement.^51^
Analgesia use (drug and approximate frequency) collected at baseline and 3, 6 and 12 months.MRI Scans (substudy of 56 patients, 6 weeks and 6 months postsurgery): see the ‘MRI substudy’ section.AEs will be collected from site reports as they occur throughout the first 12 months, and from participants in the 3, 6 and 12 months questionnaires.

Patient-reported outcome measures (OSS, WORC, EQ-5D-5L, PGIC) will be collected at 24 months as a secondary outcome, these will be published separately and will not delay publication of the primary 12-month outcome data. A detailed data management plan has been prepared following Warwick SOPs and will be available on request.

### Eligibility criteria

#### Inclusion criteria

Rotator cuff tear deemed by the treating clinician to be technically irreparable*. Many factors other than size influence whether a tear can be repaired (such as chronicity, retraction of the tendon ends, fat infiltration in muscle). However, a potential participant who has a tear that is technically repairable, such as a small tear, but is unsuitable for repair due to age or comorbidities, is not eligible for this study.Intrusive symptoms (pain and loss of function) which in the opinion of the treating clinician warrants surgery.Non-operative management has been unsuccessful. The exact nature of non-operative management will be left for the treating clinician to decide.

#### Exclusion criteria

Advanced gleno-humeral osteoarthritis (OA) on preoperative imaging (in the opinion of the treating clinician). Advanced glenohumeral OA may be interpreted as Kellgren Lawrence grade 3 or 4 changes on routine preoperative radiographs,^52^ or the MRI equivalent if radiographs have not been taken.Subscapularis deficiency* defined as a tear involving more than the superior 1 cm (approximately) of the subscapularis if repaired, or any tear that is not repaired.The treating clinician determines that interposition grafting or tendon transfers are indicated.Pseudoparalysis (an inability to actively abduct or forward flex up to 20°), as determined by the treating clinician.Unrelated, symptomatic ipsilateral shoulder disorder that would interfere with strength measurement or ability to perform rehabilitation.Other neurological or muscular condition that would interfere with strength measurement or ability to perform rehabilitation, in the opinion of the treating clinician.Previous proximal humerus fracture that could influence shoulder function, as determined by the treating clinician.Previous entry into the present trial (ie, other shoulder).Unable to complete trial procedures.Age under 18.Unable to consent to the trial.Unfit for surgery as defined by the treating clinician.

*criteria regarding whether the tear is technically repairable, and the integrity of the subscapularis, are unreliably assessed by preoperative imaging and will be reassessed in theatre prior to randomisation. People not eligible to be enrolled in the trial will be treated according to the judgement of the surgeon at the time.

### Participant identification, screening and withdrawals

Potential participants will be identified by the attending clinical team by clinicians in intermediate or secondary care clinics, or from the surgical waiting list. The attending clinician will confirm appropriateness for study eligibility based on clinical assessment and standard care preoperative imaging for that site.

All potential participants who meet the study entry criteria will be checked for eligibility and recorded on the monthly screening log. Potential participants who are willing to be approached by a suitably trained member of the research team will be provided with verbal and written information about the study, and will have the opportunity to discuss and ask questions about the study prior to informed consent being obtained.

Eligibility for the study is confirmed by the operating surgeon intraoperatively and patients may be excluded at this stage if the surgeon finds that the rotator cuff tear can be repaired. These excluded participants will be informed by letter that they are no longer taking part in the study. Baseline data will be retained to explore any differences between those who were deemed ineligible at surgery to those who were randomised.

Participants randomised into the study will be allowed to withdraw from follow-up at any time, without prejudice. This will have no effect on their current or future care.

### Randomisation

Participants are randomly allocated on a 1:1 basis to the two treatment groups via a central computer-based randomisation system provided by Warwick Clinical Trials Unit (WCTU) independent of the study team. A minimisation algorithm is used to determine participant allocation, using site, gender, age group (<70 years and ≥70 years) and cuff tear size (as assessed by the operating surgeon, ≥3 cm or <3 cm) as factors, with a random element included to provide a 70% chance that the participant will receive the treatment that minimises the imbalance, to ensure unpredictability.

Randomisation will be performed by theatre staff, after the intraoperative findings have been checked (including cuff tear size) and eligibility is confirmed. Staff use an online system in a separate room to maintain blinding, with a 24-hour back-up automated telephone system available.

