### Trial treatment(s)/intervention

#### Group 1: Standard arthroscopic debridement (control)

The control group will be an arthroscopic debridement of the subacromial space with removal of inflamed tissue (bursectomy) and unstable remnants of the torn tendon, limited bone resection of the acromion, retention of the coracoacromial ligament and biceps tenotomy (if not already torn). The anaesthetic will be left to the choice of the anaesthetist; this may include general or local anaesthesia. Surgeons may use their normal surgical technique, within the confines described in a trial specific surgical guideline (available at the trial website or at request from Warwick CTU).

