#### Group 2: Standard arthroscopic debridement plus insertion of InSpace Balloon (intervention)

Arthroscopic debridement, as described above, with insertion of the InSpace Balloon performed by subspecialty trained shoulder surgeons. The same arthroscopic debridement will be performed as described for the control group. If allocated to the balloon procedure, the company’s recommended surgical technique will be followed for sizing, insertion and deployment of the balloon, as documented in the surgical manual.

For both groups, fidelity will be assessed with an operative record form and arthroscopic photographs taken at the end of debridement and just before balloon inflation, and the number of physiotherapy visits for each participant will be documented in both arms.

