### Blinding

Treatment allocation will be blinded for both patients and assessors, only the surgical teams at the time of the operation will be aware of the allocation. Theatre staff are asked not to discuss the balloon and to communicate the allocation by using methods such as holding up a piece of paper on which the allocation is clearly written. If participants are awake, drapes are used to obscure the participant’s view and arthroscopic screens will be positioned in such a way that the patient is unable to see the procedure.

The incisions required for the two operations are similar and there is no external way in which the patients will be able to detect the presence or absence of the balloon, except for the size of the lateral portal. One of the incisions (the lateral portal) will need to be slightly larger to insert the balloon—1.5 cm as opposed to 1 cm. A 1.5 cm incision will be used for all participants, which is a very small change from standard care and is very unlikely to have a negative effect on any participant. Incisions will therefore be the same for both groups.

The operation note will be blinded to prevent accidental unblinding of the patient (eg, in the discharge information or during postoperative physiotherapy). A standard recommended operation note template will be given to all sites adjusted to fit their local operation note systems. The details of the operation related to the balloon will be recorded in a secure online form easily accessible to the surgeon.

Unblinding may very rarely be required in an emergency situation, such as an overnight admission for suspected postoperative infection. Unblinding will be performed only by NHS staff in an emergency situation, by using a predefined web-based system, from a link inserted in the operation note. A two-way secure verification process will be performed using email, and an access code will be emailed only to an active NHS email address. A full explanation of the clinical circumstances and the need for access to data will be requested by the trial team for audit and monitoring purposes from the person who performed the unblinding, and the principal investigator for the site will be informed. The system has been designed and tested by the WCTU programming team to ensure that it is both secure and fully functional.

Participants will be asked at the 12-month time point, after collection of the primary outcome, if they were aware of their allocation.

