### MRI substudy

Participants selected for inclusion in the MRI substudy will undergo two research MRI scans at 8 weeks and 6 months post-operatively. MRI scans were preferred to X-rays for this purpose as measures taken from X-rays would be prone to error, primarily due to variation in the angle between the shoulder joint and the beam of the X-ray. This will assess the mechanism of action of the balloon, when the balloons are likely to be still inflated (but when acute postoperative pain has subsided), and when they are likely to have fully deflated, to see if the proposed mechanism for ongoing improvement is maintained. Passive imaging alone will not be adequate to demonstrate the function of the balloon and imaging will also need to be performed when the deltoid muscle is active, producing a proximally directed force on the humerus.^53 54^

For this study, we have developed (and piloted) a novel dynamic approach to assessing the function of the rotator cuff using MRI imaging under a mild deltoid load, to specifically assess the mechanism of the balloon. A separate paper on the pilot study for the trial is in preparation and will describe these methods in more detail.

All participants will be eligible (unless they have a contraindication to MRI, or do not want to take part in the substudy), but the substudy will only be undertaken at a proportion of participating sites. The primary outcome will be the minimum acromiohumeral distance on the ‘deltoid-active’ coronal sequences at 6 months, a reliable and proven measure.^55–57^ The balloon is expected to have deflated by 6 months.^58^ Secondary measures will be acromiohumeral distance on passive images, and the change in acromio-humeral distance between active and passive images. The position of the balloon will be assessed to check for migration and consistency of placement relative to the acromion.

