### Statistical analysis plan

All data will be analysed and reported in accordance with the Consolidated Standards of Reporting Trials (CONSORT) guidelines.^62 63^ A detailed statistical analysis plan and a data sharing plan will be agreed with the DMC prior to any formal analyses being conducted.

Baseline data will be summarised to check comparability between treatment arms. Standard statistical summaries (eg, means and SD, dependent on data type) will be presented for the primary outcome measure and all secondary outcome measures.

The primary analysis will investigate differences in the OSS 12 months after surgery between the two treatment groups. It will be conducted on an intention-to-treat basis following the methods, test statistics and boundaries described by Parsons *et al*.^38^ To preserve the integrity of the study, the exact boundaries used for testing are given in the adaptive charter known only to the study team and independent DMC. Briefly, if the study recruits to target, the method set out by Parsons *et al*
38 will be used to calculate the boundaries and if the study stops early, testing will proceed using boundaries calculated by the deletion method for overrunning analysis, described by Whitehead, with clinical inferences following directly from widely used methods for unbiased estimates and confidence intervals in group sequential trials.^64–66^

The primary analysis will be augmented by calculating adjusted estimates of treatment group differences (with 95% CIs) for the OSS using a mixed-effects model. The mixed-effects model will include a random effect for the recruiting centre, and fixed effects for the variables of interest included in the minimisation algorithm, patient age, gender and size of tear. In addition, subject to the observed data, sensitivity analyses such as per-protocol analyses or multiple imputation will also be undertaken. If undertaken, all multiple imputation assumptions will be justified and reported. Estimates of efficacy for the other outcome measures will follow this approach to analysis.

Prespecified subgroup analyses will be undertaken to assess whether there is evidence that the intervention effect differs with respect to:

The size of the rotator cuff tear as measured at the start of surgery, defined as large or massive cuff tear (≥3 cm) or moderate to small (<3 cm).Gender.Age (>70 or <70).

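### The randomisation rule lets the surgeon learn the allocation before the common debridement is finished, so an unintended difference in debridement between arms is possible

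*Protocol article*

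**What the plan says.** The Randomisation section of the protocol article ties randomisation to two conditions: "Randomisation will be performed by theatre staff, after the intraoperative findings have been checked (including cuff tear size) and eligibility is confirmed". Completion of the debridement is not among them. For the first condition, the subgroup list in the Statistical analysis plan section describes the tear-size factor as follows: "The size of the rotator cuff tear as measured at the start of surgery".

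The Blinding section states that "only the surgical teams at the time of the operation will be aware of the allocation". Theatre staff are asked to "communicate the allocation by using methods such as holding up a piece of paper on which the allocation is clearly written". That section does not link disclosure to any stage of the operation.

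The control procedure consists of bursectomy, removal of unstable tendon remnants, and "limited bone resection of the acromion, retention of the coracoacromial ligament and biceps tenotomy (if not already torn". On latitude, the same section says: "Surgeons may use their normal surgical technique, within the confines described in a trial specific surgical guideline". For the balloon arm the article says: "The same arthroscopic debridement will be performed as described for the control group". Fidelity in both arms is to be assessed from an operative record form and from arthroscopic photographs, including one when debridement ends. The Introduction places balloon insertion at the end of the debridement.

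The trial's primary outcome is the OSS at 12 months. For the MRI substudy: "The primary outcome will be the minimum acromiohumeral distance on the ‘deltoid-active’ coronal sequences at 6 months".

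**The concern.** The trial compares debridement plus balloon with debridement alone. The contrast isolates the balloon only if the debridement is the same in both arms. Several of its parts are matters of degree: how much bursa and tendon remnant to remove, and how much bone to take within a limited resection. A surgeon who already knows the allocation might, without meaning to, debride more fully when no balloon will follow, or clear more space when one will. Either pattern, if consistent, would be mixed into the estimated balloon effect.

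Blinding of participants and assessors does not close this route, because it acts through the surgery and not through outcome assessment. The MRI substudy has a further exposure. Its outcome is a distance measured from the acromion, and the debridement may remove acromial bone. Both research scans are postoperative, so the article describes no research scan before surgery that could separate bone removed from balloon effect.

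**Working it through.** **1. Order of events that the article allows**

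| Step | What the article fixes | Section |
|---|---|---|
| Tear size measured | Start of surgery | Statistical analysis plan |
| Repairability and subscapularis reassessed | In theatre, before randomisation | Exclusion criteria |
| Randomisation | After the two steps above; no later condition | Randomisation |
| Surgeon told the allocation | In theatre; stage not given | Blinding |
| Debridement, with acromial resection | Not placed before or after randomisation | Group 1 (control) |
| End-of-debridement photograph | When debridement ends | Group 2 (intervention) |
| Balloon insertion | At the end of debridement | Introduction |

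The Randomisation section therefore sets an earliest point. A site that randomises before the debridement complies with it, and so does a site that randomises afterwards. Because the balloon goes in last, nothing in the article requires the surgeon to know the allocation during the debridement.

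**2. The plan's own figures (Power and sample size section)**

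- OSS, fixed design: difference 6, SD 12, 90% power, two-sided 5%. Per arm n = 2 × (1.960 + 1.282)² × (12/6)² = 84.1, rounded up to 85, so 170 in total. The plan states 170.
- OSS, adaptive design: 188/0.85 = 221.2. The plan states 221. The 188 comes from simulation and cannot be rebuilt from the article.
- MRI: difference 1.5 mm, SD 1.72 mm, 80% power, two-sided 5% (sidedness assumed). A t-test needs 22 per arm, 44 in total; 44/0.8 = 55. The plan states 56, which is close.

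No figure in the plan is in dispute. They serve only as inputs to the next step.

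**3. Illustration of what a systematic shift would do**

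The documents do not give the size of any debridement effect, so the shift b is an assumption. The calculation uses a two-sided 5% normal test in a fixed design and ignores the interim looks.

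- Standard error: SE = SD × √(2/n).
- Rejection probability with no true balloon effect: 1 − Φ(1.96 − b/SE) + Φ(−1.96 − b/SE).
- Power at a true 6-point benefit when the shift acts against the balloon: 1 − Φ(1.96 − (6 − b)/SE).

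OSS with 188/2 = 94 per arm: SE = 12 × √(2/94) = 1.75.

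| Assumed shift b (points) | Rejection rate, no true effect | Power at true 6 points, shift against balloon |
|---|---|---|
| 0 | 5.0% | 92.9% |
| 0.5 | 5.9% | 88.1% |
| 1 | 8.8% | 81.5% |
| 2 | 20.8% | 62.8% |
| 3 | 40.3% | 40.3% |

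MRI after 20% loss: 56 × 0.8/2 = 22.4, taken as 22 per arm; SE = 1.72 × √(2/22) = 0.52 mm.

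| Assumed shift b (mm) | Rejection rate, no true effect |
|---|---|
| 0.25 | 7.7% |
| 0.5 | 16.1% |
| 1.0 | 48.7% |

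Shifts of 1 to 2 points and of 0.25 to 0.5 mm are one sixth to one third of the respective target differences (6 points and 1.5 mm). The tables show how sensitive the tests would be. They are not estimates of what will happen.

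**The case against.** The strongest reply is that the article is a condensed account and that the order of steps within an operation belongs in the full protocol or the surgical guideline, neither of which is shown. A reader might infer that the plan orders randomisation before debridement. It does not: the wording gives an earliest point and is equally true of a site that randomises at the end. A reader might also infer that eligibility is always settled before any tissue is removed. Only tear size is tied to the start of surgery. How much surgery precedes a finding of irreparability is not stated, and the subscapularis criterion depends partly on whether a tear is repaired.

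Nor is the extent of debridement simply left to the surgeon. Normal technique is allowed only within the trial guideline, the resection is described as limited, the ligament is retained, and the balloon arm must receive the same debridement. The record form and photographs are a planned check on exactly this.

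The bias sizes are assumed inputs. The two behaviours described run in opposite directions and would partly cancel if surgeons differ. No passage shows that the OSS responds to the extent of debridement, or that resected bone translates one for one into deltoid-active distance.

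All of this stands, and it limits the strength of the point. It does not remove it. The article states a rule for when to randomise, and that rule permits early disclosure to an unblinded operator. The instruction, form and photographs standardise and record the debridement; they do not conceal the allocation while it is done.

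**Conclusion.** The point holds as a possibility that the stated rule leaves open. The surgeon may know the allocation during some or all of the debridement, and an unintended difference between arms could follow, within limits set by a guideline that is not shown. The OSS could be affected, and acromial resection could also affect the MRI distance. Direction and size are unknown.

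A reader might take the tables to mean that the trial's error rate is 9% to 21%. The documents do not support that: those values need a consistent shift of 1 to 2 points, for which there is no evidence here, and they ignore the group sequential boundaries. The documents also do not show that debridement differs by arm at any site.

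The conclusion rests on three things the article does state: the two conditions for randomisation, the unblinded surgical team, and balloon insertion at the end of debridement. A rule that closes the route is available at little cost, so this is more than a request for detail. If the guideline already delays disclosure until debridement is complete, what remains is a wording mismatch with the Randomisation section.

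**What to change.** Amend the Randomisation section so that randomisation, or at least disclosure of the allocation to the surgeon, takes place only after eligibility is confirmed, the debridement is complete and the end-of-debridement photograph has been taken. Record the times of the photograph and of randomisation (or of disclosure, if that is what is delayed), so that compliance can be reported. If the surgical guideline already requires this order, align the Randomisation section with it.

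For participants already randomised, compare the debridement components by arm from the existing operative forms and photographs.

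This changes when the allocation is disclosed and nothing about surgical technique, sample size, power or type I error. The cost is an amendment, brief site retraining while recruitment is under way, and a wait of a few minutes late in the operation. The online system in a separate room is already in use. Participants will have been randomised under two rules, so the report should give the date of the change.
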